## Introduction

It is well-known that large cohort studies play essential roles in gaining knowledge about diseases and reducing their associated burden (1). Stroke, ischemic heart disease, and traffic injury are the top three leading causes of years of life lost (YLLs) in China (2). The risk factors contributing to the loss of disability-adjusted life-years include inappropriate dietary habits such as high sodium consumption (15.9%), hypertension (13.3%), tobacco use (12.5%), and air pollution (9.3%) (3). The area around the capital of China, called the Beijing–Tianjin–Hebei (BTH) region, is the political, economic, and cultural center of China. In the BTH area, ischemic heart disease is the leading cause of YLLs, and inappropriate dietary habits result in high sodium consumption. In 2016, the “Healthy China 2030 Plan” was launched by the State Council. According to this plan, health-related risk factors for non-communicable diseases (NCDs) will be under effective control by 2030, including an increase in the proportion of individuals taking physical exercise and a reduction in the per-capita daily salt intake by 20% (4). As residents in the BTH area may experience a significant change in lifestyle risk factors in the next few decades, a cohort study is necessary to explore the effect of health determinant changes on NCDs and to demonstrate the effect of changes due to health-related strategies.

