### Outcomes of Interest

Number of deaths and cause of death.Incident of major NCDs, such as hypertension (*ICD-10*: I10-I15), diabetes (*ICD-10*: E10-E14), ischemic heart disease (*ICD-10*: I20-I25), cerebrovascular disease (*ICD-10*: I60-I69), chronic obstructive pulmonary disease (*ICD-10*: J44), and cancer (*ICD-10*: C00-C97).Intermediate phenotypes or key risk factors for NCDs, including anthropometric factors and physiological, lifestyle, and environmental factors.

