**Figure 3 F3:**
[figure not shown]
Flowchart of the baseline survey in CHCN-BTH.

Suitable places for the field survey were selected after consideration of the space needed for the survey instruments and the waiting space needed for the survey subjects. For example, we selected community healthcare centers or temporarily requisitioned schools near community healthcare centers as survey places. Face-to-face interviews will be performed using a uniform questionnaire. To ensure the accuracy of the questionnaire information, all questionnaires will be verified by the inspectors. The questionnaire includes five sections: sociodemographic characteristics, familial and personal medical history, lifestyle behaviors (including drinking, smoking, physical exercise), pollutant exposure (passive smoking condition and air pollution exposure condition), and psychological conditions. Current smoking was defined as smoking at least one cigarette per day in the last 6 months. Former smoking was defined as smoking less than one cigarette per day for at least 6 months. Alcohol drinking was defined as accumulatively drinking wine/liqueur more than 250 g/year or drinking beer more than 5 L/year (24). Physical exercise was defined as participating in moderate or vigorous activity for at least 30 min each time and at least once per week. Information on psychological conditions was collected using the Depression, Anxiety and Stress Scale-21 (25, 26). The scale includes three subscales, and each subscale contains seven items. The details of the questionnaire are shown in Table 2.

**Table 2 T2:** Sections and topics of the questionnaire.

**Type of data**	**Components**
Sociodemographic characteristics	Sex, age, ethnicity
	Residence address
	Cellphone number
	Personal income, education, occupation
	Menstrual history
Personal and family disease history	Hypertension (date of diagnosis, medication)
	Diabetes (date of diagnosis, medication)
	Cardiovascular disease (date of diagnosis, medication)
	Respiratory disease
	Gastrointestinal disease
	Cancer
	Others
Lifestyle behaviors	Tobacco use and smoking
	Alcohol consumption
	Labor intensity
	Physical activity/frequency
Outdoor exposure	Outdoor activity/frequency
	Window opening frequency
	Protective measurements during smog:
	Stay indoors/mask wearing/usage of air purifier
Indoor air pollution exposure	Passive smoking
	Cooking fuel type, cooking frequency
	Cooking habits:
	Kitchen door opening/usage of smoke extractors

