### Statistical Plan

All potential risk factors and outcomes will be described at baseline and at each follow-up. Normally distributed continuous variables will be summarized by the mean and standard deviation, and skewed distributed continuous variables will be described by the median and interquartile range. To compare possible differences between two groups, an independent-samples *t*-test will be used for qualitative variables with a normal or skewed distribution, and the χ^2^-test will be used for categorical variables. The χ^2^-test will be used for categorical variables in the description of the profiles of the responders and non-responders. When comparing differences among more than two groups, the Kruskal–Wallis test will be used for continuous variables, and one-way analysis of variance will be used for quantitative variables. Trajectory analysis will be used to explore the effect of risk factor changes on NCDs.

Generalized additive mixed models will be used to examine the associations of long-term air pollutant exposures with physiological indicators and the prevalence of NCDs. The exposure assessment during the follow-up period will use a time-spatial continuous prediction model. Time-dependent Cox proportional hazards models will be used to analyze the associations of air pollutant exposures with the incidence of NCDs. A penalized cubic regression spline of air pollutants will be included in the models to explore the non-linear exposure–response relationships.

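### As written, the former-smoking rule requires neither past regular smoking nor quitting, so no reading of it isolates ex-smokers

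*Protocol article*

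**What the plan says.** The questionnaire paragraph of the Measurements section, after Figure 3, gives two smoking definitions one after the other. The first is "Current smoking was defined as smoking at least one cigarette per day in the last 6 months". The second is "Former smoking was defined as smoking less than one cigarette per day for at least 6 months". No definition of a never smoker or an occasional smoker appears anywhere in the article. Table 2, which lists questionnaire topics only, has a single entry for this subject: "Tobacco use and smoking".

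The article gives smoking some weight. The Introduction puts tobacco use at 12.5% of lost disability-adjusted life-years, behind dietary habits (15.9%) and hypertension (13.3%) and ahead of air pollution (9.3%). Table 1 has lifestyle behaviors collected at baseline, at follow-up and at the repeated measurements. The Objectives cover etiology with lifestyle taken into account, and risk prediction models. The Statistical Plan adds trajectory analysis of changing risk factors and says: "Time-dependent Cox proportional hazards models will be used to analyze the associations of air pollutant exposures with the incidence of NCDs". It lists no adjustment covariates.

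**The concern.** A former smoker is ordinarily someone who once smoked regularly and then stopped. The stated rule contains neither element. It only sets a ceiling on consumption over a period, and people with quite different histories sit under that ceiling.

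The outcomes include ischemic heart disease, cerebrovascular disease, "chronic obstructive pulmonary disease (*ICD-10*: J44), and cancer (*ICD-10*: C00-C97"). Smoking history is a natural exposure of interest for these, a candidate predictor and a potential adjustment variable. If the former group mixes ex-smokers with people who never smoked regularly, its estimated effect is likely to be pulled toward no effect, and adjusting for it would only partly account for past smoking.

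The error would also recur in the follow-up data. A daily smoker who cuts down below one a day without stopping would move from current to former, and a trajectory analysis would read that as quitting.

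**Working it through.** The article gives no smoking frequencies, so there is no figure to reproduce. The check applies the two written rules to typical smoking histories.

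**Step 1: classification.** Reading A takes the words literally, so zero cigarettes counts as less than one a day. Reading B takes the word smoking to require more than zero.

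| History | Reading A | Reading B |
|---|---|---|
| Never smoked | former | not former |
| Quit completely 5 years ago | former | not former |
| Occasional for years, 3 a week (3/7 = 0.43 a day) | former | former |
| Was daily, cut down below one a day for over 6 months, still smoking | former | former |
| 10 a day throughout | current | current |
| 10 a day, quit 3 months ago | not former | not former |

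Only Reading B keeps never smokers out, and it also drops the complete quitter, whom the category should contain. The third and fourth rows are former under both readings. The last row is current if the six-month window in the current-smoking rule means at any time within it, and belongs to neither category if it means throughout. The text does not say which.

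**Step 2: illustrative size under Reading A.** All shares are assumptions and none comes from the article.

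Never smokers as a share of never plus true former smokers = never / (never + former):
- 60% never, 10% former: 60/(60 + 10) = 86%
- 75% never, 5% former: 75/(75 + 5) = 94%

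Occasional smokers can be added, over a wider assumed range. True ex-smokers as a share of the literal former group = former / (never + former + occasional):
- 75%, 3%, 2% (never, former, occasional): 3/80 = 4%
- 65%, 7%, 3%: 7/75 = 9%
- 55%, 12%, 5%: 12/72 = 17%

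**Step 3: the same shares if a filter removes never smokers first.** True ex-smokers = former / (former + occasional): 3/5 = 60%, 7/10 = 70%, 12/17 = 71%.

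**Step 4: rough dilution.** Assume a hazard ratio of 1.5 for true ex-smokers and 1 for everyone else in the group, both against true never smokers. The group value is about 1 + 0.5 × (share of true ex-smokers):
- Reading A: 1 + 0.5 × 0.0375 = 1.02 up to 1 + 0.5 × 0.167 = 1.08
- With the filter: 1 + 0.5 × 0.60 = 1.30 up to 1 + 0.5 × 0.706 = 1.35

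The first pair is notional, because Reading A leaves no separate never-smoker group to serve as the reference.

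**The case against.** The strongest reply is that the defined term is former smoking and follows directly on current smoking, so a reader will supply the missing condition that the person once smoked. The article is also a condensed account. The uniform questionnaire is not shown, Table 2 lists topics only, and an ever-smoked question may well come before this item. That Reading A would leave no never-smoker group makes such a filter plausible.

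Much of this stands. A reader might infer that never smokers have actually been coded as former in the cohort data. The article does not show that; it shows only what the published rule would do if applied as written. The 86-94% is likewise not an estimate for this cohort, since it rests on assumed shares, the literal reading and no filter.

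Other stronger claims also lack support. The article does not call smoking the main confounder, lists no covariates, and gives no smoking rates by site, so bias of a given size in the pollutant effects cannot be derived from it. A firm claim that recent quitters fit neither category depends on one reading of the six-month window. Current daily smokers remain identifiable throughout.

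The charitable reading still does not repair the rule. An ever-smoked filter leaves long-term occasional smokers in the former group. Even a requirement of past regular smoking leaves in those who cut down without stopping, because nothing in the rule asks for cessation.

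**Conclusion.** The point holds as a defect in a stated definition. It is not a complaint about missing detail: the article gives a rule, and neither reading of its words isolates ex-smokers. Applied as written, it classes occasional smokers and daily smokers who cut down as former under both readings. It classes never smokers as former only under the literal reading and only if the questionnaire has no ever-smoked filter.

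The likely consequences are a diluted former-smoking effect and incomplete adjustment for past smoking where smoking is used as a covariate. The size cannot be taken from the article. Under the assumed shares above, true ex-smokers would make up 4-17% of the former group at worst and 60-71% if never smokers are filtered out. The correction should be made, because the article itself ranks tobacco use among the leading risk factors and smoking is re-collected through follow-up. It changes no design figure.

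**What to change.** Replace the two definitions with four exclusive and exhaustive categories, where regular means one or more cigarettes a day, assigned in this order:

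1. **Current:** any regular smoking within the preceding 6 months. This explicitly includes people who quit during that window.
2. **Occasional:** some smoking within that window, but none of it regular. Flag separately, with a marker for past regular smoking so that people who cut down can be told apart.
3. **Former:** past regular smoking, then no cigarettes for 6 months or longer.
4. **Never:** no past regular smoking and none in that window.

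If the questionnaire already has an ever-smoked filter, state it next to the definitions. Recode baseline status from the recorded tobacco items. Where those items do not establish past regular smoking or cessation, ask at the next two-yearly telephone interview, which already collects lifestyle changes. Apply the same rule at every later round so that changes in status are comparable.

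The cost is a recoding exercise and at most one or two added interview items. History obtained later will carry some recall error, which is a small price compared with leaving the category undefined.

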### Follow-Up

Community-based participants will be followed up every 2 years. All of the participants will be followed up by telephone-based interviews. Several methods will be used to achieve the goal that the overall follow-up rate should be more than 90%. Ways to guarantee a high follow-up rate are as follows: (1) For each participant, we will conduct telephone interviews on both workdays and weekends to ensure they can answer the telephone at least once. (2) For participants who cannot be contacted by telephone, a household survey will be conducted according to their baseline home address. (3) For participants who could not be contacted by telephone or household surveys, medical records in community healthcare centers will be acquired to confirm their health status and to collect information on BP, weight, and fasting blood glucose. (4) Death surveillance is generally based on the Disease Surveillance Point (DSP) system. For places not covered by DSPs, community healthcare centers will help to collect medical certificates of death. Photos of death certificates will be named “ID+name of participants” and collected by the research group. (5) Subjects will be deemed lost to follow-up if they cannot be contacted by telephone or household survey, and their medical or death records are not accessible. Information on home address changes, self-reported disease status, and its potential determinants will be collected in the follow-up survey through telephone interviews or household surveys. The expected proportion of participants lost to follow-up is <10%. We will recruit new participants in their community to replace the lost participants, matching by age and sex.

Among the participants interviewed by telephone in the follow-up survey, we will randomly select 1% to conduct the survey again at each survey site. If the proportion of inconsistent information from the above two surveys is >10%, all of the participants at that survey site will be resurveyed. For all the community-based participants, BP, disease status, and serum markers (fasting glucose, total cholesterol, triglyceride, low-density lipoprotein cholesterol, and high-density lipoprotein cholesterol) will be accessed through medical records in community hospitals during follow-up survey. The minimum proportion of repeated measurements among community participants will be 20% at each follow-up. All participants will be examined after five rounds of follow-up surveys. For participants who undergo employee physical examinations, serum markers and physical examination exactly the same as baseline will be examined every 2 years. The follow-up procedure is shown in Figure 4.

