Physical examinations will include assessments of BP, heart rate, grip strength, oxygen saturation, body composition, bone mineral density, ECG, and lung function. BP will be measured with a digital sphygmomanometer (OMRON HEM-907, Japan) after resting in a seated position for at least 10 min. Measurements will be recorded three times with 1-min intervals, and the mean SBP and DBP will be recorded. Body composition will be measured in the upright position after fasting and urinating with their arms naturally hanging by using a body composition analyzer (TANITA BC-420, Japan). Resting ECG will be performed in the supine position after sitting quietly for 5 min. A standard 12-lead ECG will be acquired digitally using a Mortara ECG machine (Mortara Eli 250c, Milwaukee, WI, USA) at a calibration of 10 mm/mV and a speed of 25 mm/s. Bone mineral density will be measured in a seated position using an Osteospace Pegasus ultrasound bone densitometer (MEDILINK, France). Bone mineral density measurements will be conducted on the participant's bare right ankle and foot by using a Pegasus device (MEDILINK, France). Lung function measurement (spirometry) will be conducted using a portable spirometer (CareFusion MasterScreen Pneumo, Germany) according to the guidelines issued by the American Thoracic Society (27). All physical examinations will be carried out by trained staff based on a standard manual, and all of the measurement equipment will be regularly calibrated. Details of the physical examination measurements are shown in Table 3.

**Table 3 T3:** Physical examination measurements and laboratory test.

**Measures**	**Measuring equipment**	**Variables**	**Times of measurements**
Blood pressure	OMRON HEM-907, Japan	Systolic pressure (SBP, mmHg), diastolic blood pressure (DBP, mmHg)	3
Body composition	TANITA BC-420, Japan	Height, cloth weight, weight, reference value of weight, fat mass rating (fat%), reference value of fat%, fat mass, reference value of fat mass, fat-free body mass, muscle mass, reference value of muscle mass, muscle mass rating, bone mass, reference value of bone mass, body water, reference value of the body water, the body water rating, reference value of the body degree, body mass index (BMI), standard weight, obesity degree, visceral fat rating, the basic metabolic rate, the basic metabolic rate, basal metabolism, metabolism age, and impedance	1

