Classic cohort studies generally focus on certain types of exposure factors and certain types of diseases. The current cohort will not only focus on traditional lifestyle risk factors but also investigate dietary habits, mental health, environment, genetics, and epigenetics so that the etiology of common chronic diseases can be demonstrated comprehensively. Given that many chronic diseases share common pathogenic pathways, the current cohort will systematically analyze multiple exposures and their effects on diseases based on genomics, proteomics, and metabolomics to identify the specific and shared pathways of related diseases. For data collection, in addition to those based on previous traditional chronic disease management modes, this project will explore new methods to achieve real-time dynamic data monitoring and automatic data collection. For example, we will use an ID card reader to collect the subject's ID number, sex, birthday, and living address automatically and save the above information in an Excel table. The participants will be identified by the patient's ID number from the health management records in community healthcare centers, and their medical information will be collected and updated dynamically. Electronic information acquisition systems based on mobile terminals will play important roles not only in obtaining health-related big data but also in health management in the community. Moreover, 20% of the participants will be repeatedly measured in the follow-up visits, which offers an opportunity to conduct trajectory analyses to determine the dynamic patterns of risk factors contributing to the disease.

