There are several limitations of the current cohort. First, the survey sites and the participants will not be randomly chosen. This is because the current study focuses on selected survey sites with various economic, medical, and environmental characteristics to better demonstrate the pathogenic mechanism of NCDs. In the central functional district of Beijing, we selected Chaoyang district. Tianjin and Shijiazhuang are in good terms of social economics with moderate air pollution, while Baoding is a city with moderate economic status and severe air pollution. Chengde city was selected as having better air quality. Xiong'an city may experience rapid economic development in the next 5 years. The residents' socioeconomic level and lifestyle may undergo tremendous changes, which may have a certain impact on health. Moreover, instead of estimating the prevalence of diseases by representative sampling, this cohort study is more concerned about the proportion of participants who could be followed up. Thus, we chose stable communities and participants to ensure a good follow-up rate. During the study recruitment process, the investigator will explain that enrollment in the cohort requires continued follow-up. Subjects who actively choose to join the cohort may have a stronger willingness to participate compared with randomly chosen participants, which may avoid loss to follow-up. Second, the current cohort will exclude participants with major physical and mental disabilities and any who could not complete the survey even with the help of investigators. These exclusion criteria may lead to a “healthy cohort” effect, and the results of this cohort study will be more applicable to a healthier population and should be explained and extrapolated with caution. Third, most of the surveys will be conducted on workdays, and elderly people and retirees may prefer to participate compared with young people and employees, which may introduce selection bias. To reduce selection bias and better represent the target population, we will recruit participants considering their demographic structure according to the results of the sixth national census. Finally, the same examination equipment will be used for physical examination to ensure the comparability of measurements. Because of the limited quantity of equipment, it is not possible to carry out repeated measurements at the same time. Therefore, in this study, only 20% of the subjects were repeated measured in each time of follow-up. It was planned to complete repeated measurements of all the subjects after five rounds of follow-up. In order to overcome the shortage of partial repeated measurements, telephone interviews and medical records update will be conducted to all participants every 2 years to obtain the change of lifestyle behavior and other health determinants.

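### Community members average about one study-standard re-examination in ten years against five for employees, with record values in between, so measurement source and case detection need to be modelled

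*Protocol article*

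**What the plan says.** The Follow-Up section sets a two-yearly cycle: "Community-based participants will be followed up every 2 years". On standardised re-examination it says "The minimum proportion of repeated measurements among community participants will be 20% at each follow-up", with everyone examined after five rounds. The limitations part of the Discussion gives the same share as a ceiling set by equipment, "only 20% of the subjects were repeated measured in each time of follow-up", and adds "It was planned to complete repeated measurements of all the subjects after five rounds of follow-up". The Table 1 footnote speaks instead of a selected subgroup that repeats the measurements every two years. The Discussion also says that 20% are measured repeatedly, "which offers an opportunity to conduct trajectory analyses to determine the dynamic patterns of risk factors contributing to the disease".

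For all community participants, blood pressure, disease status and five serum markers (fasting glucose and four lipids) "will be accessed through medical records in community hospitals during follow-up survey". Baseline was different. The Measurements section prescribes one blood pressure device and "Measurements will be recorded three times with 1-min intervals, and the mean SBP and DBP will be recorded", and serum was tested on one analyser in one hospital laboratory. For participants recruited through employee physical examinations, "serum markers and physical examination exactly the same as baseline will be examined every 2 years".

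The Statistical Plan includes trajectory analysis of risk-factor change, mixed and generalized additive mixed models for physiological indicators and biomarkers, and time-dependent Cox models for incidence. Self-reported incident disease is followed up through records and ascertained by an event committee.

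**The concern.** Two features of the follow-up could distort the analyses.

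**Source is tied to time.** Community members move from a research measurement at baseline to mostly routine measurements afterwards. Any systematic difference between the two methods enters the data as a change since baseline, over the same years in which pollution is falling and regional policy is changing. Those are the changes the study wants to evaluate. The Discussion offers record updates as the remedy for sparse re-measurement, and that remedy is what introduces the change of source.

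**Examination intensity is tied to recruitment source.** Hypertension, diabetes and COPD can go unnoticed. A group examined every two years will yield more of these diagnoses than a group examined about once in ten years, whatever the true incidence.

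The claim about trajectories is a further point. If the typical community member has two study-standard points, these give a difference but not the shape of an individual course.

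**Working it through.** **Inputs.** From Study Design and Settings: 30,000 community and 6,000 physical-examination participants. From Follow-Up: at least 20% of community participants re-measured per round, two-year interval, five rounds to full coverage, and employees fully re-examined each round.

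**1. Coverage (reproduces the plan's own figure).** Share per round × rounds = 20% × 5 = 100%, over 5 × 2 = 10 years. The mean number of study-standard re-examinations is therefore 1.0 per community member and 5 per employee. With baseline, that is 2 against 6 time points.

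**2. Balance of the standardised follow-up data.** Per round, 30,000 × 0.20 = 6,000 community examinations and 6,000 employee examinations. Employees are 6,000/36,000 = 17% of the cohort but 6,000/12,000 = 50% of the standardised follow-up examinations. The remaining 1 − 0.20 = 80% of community person-rounds have no study-standard value.

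**3. How far this depends on the selection rule.**

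| Reading of the 20% | Re-examinations per community member over five rounds |
|---|---|
| Rotating to full coverage (Follow-Up, limitations) | one each |
| Fixed subgroup (possible from the Table 1 footnote and the trajectory sentence) | five for 6,000; none for 24,000 until a final examination of all |
| Independent 20% draw each round | none: 0.8^5 = 33%; one: 5 × 0.2 × 0.8^4 = 41%; two or more: 26% |

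The 20% is a minimum. At 40% per round the mean would be 0.40 × 5 = 2.0.

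**4. Spurious change in blood pressure (assumed offsets, not in the documents).** Suppose record systolic pressure differs from the study method by a constant d, nothing truly changes, and every community member not examined in a round has a record value. The mean apparent community change is 0.80 × d:
- d = 1 mmHg gives 0.8 mmHg
- d = 2 mmHg gives 1.6 mmHg
- d = 5 mmHg gives 4.0 mmHg

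The corresponding figure in employees is 0, because their method does not change.

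**5. Detection of silent disease (assumptions).** Take onset as uniform over ten years, one community examination at year 2, 4, 6, 8 or 10 with equal chance, and every examination finding disease already present. The community examination then finds (2+4+6+8+10)/5 ÷ 10 = 60% of silent onsets, against 100% in employees by year 10. If records and self-report find a share s of the remainder, the community figure is 0.60 + 0.40s: 70%, 80% and 90% for s = 25%, 50% and 75%.

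**6. What records do not cover.** The record list for all community participants is blood pressure, disease status and five serum markers. For contacted participants no record substitute is stated for spirometry, ECG, bone density, body composition, grip strength, oxygen saturation or the other serum markers. Between examinations those values are simply absent.

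**The case against.** Several stronger readings are tempting, and the document does not support them.

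- **That community members get exactly one re-examination.** The 20% is a floor, and two places can be read as a fixed panel with many repeats. This stands: one is an average at the minimum. The limitations text does present 20% as what the equipment allows, so a materially higher share cannot be assumed.
- **That source differences will be taken for real change.** Nothing says record and study values will be pooled without regard to source, and handling of source may sit in an analysis plan that is not shown. Records are sought for every community member, including those re-examined, so paired values for calibration should exist wherever a record is available. What the article does fix is the mixed-source design itself, so the supportable wording is that change may appear unless source is modelled.
- **That trajectory analysis is impossible.** Lifestyle behaviours are collected from everyone at each round, so those trajectories are unaffected. Staggered repeats can also inform a population-average curve. What two points cannot show is individual shape for examined measures.
- **That comparisons between exposure areas are biased by a known amount.** An offset common to all sites would not by itself bias between-site contrasts. The effect of unequal detection depends on how employees are spread over sites, which is not stated.

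Two mitigations deserve weight. The authors disclose the partial repeats and give a reason, but their remedy does not address comparability of sources. Committee adjudication reduces misclassification of reported events, but it starts from self-report and records and cannot find disease that neither has registered.

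**Conclusion.** The point holds in a limited form and is worth correcting. At the stated minimum and with rotation, community members average one study-standard re-examination in ten years against five for employees, and about 80% of community person-rounds rest on records for blood pressure, glucose and lipids. Followed as written, this links measurement source to time and detection of silent disease to recruitment source.

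The sizes are conditional. The spurious mean change of 0.8 to 4.0 mmHg rests on assumed offsets of 1 to 5 mmHg and complete records. The 60% to 90% detection range rests on uniform onset, one examination at a random round, and record or self-report capture of 0% to 75% of the remainder. Neither is an estimate for this cohort. The direction of the detection difference is well founded; its effect on exposure contrasts cannot be sized from the document. The statements on fixed or rotating re-measurement must be reconciled.

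**What to change.** 1. State whether the re-measured 20% is a fixed panel or rotates, bring the Table 1 footnote, Follow-Up and Discussion into line, and draw each selection at random within site.
2. Record the source of every blood pressure and serum value. Before pooling in mixed, generalized additive mixed or trajectory models, calibrate record values by site on community participants who have both a study and a record value, and keep a source indicator in the model.
3. Report a sensitivity analysis using study-standard values only.
4. Stratify the incidence Cox models by recruitment source (community or employee), with a sensitivity analysis limited to record-confirmed, committee-adjudicated diagnoses. The committee definition alone does not equalise detection, so the stratification is needed as well.
5. Limit the Discussion's claim on individual trajectories of examined measures to participants with at least three study-standard measurements, from either recruitment source. Restricting it to employees would discard valid community data. Interview-based lifestyle trajectories need no change.

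The cost is protocol wording, a calibration step and some extra analysis, with less precision for individual trajectories of examined measures. No additional examinations are required.
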